**Adult reading test 2nd edition (ART-2):** The Adult Reading Test 2nd Edition (ART-2) (Adult Reading Test Ltd, Hayling Island, 2017) will provide participants with a ‘naturalistic’ passage of text to be read aloud [67] with and without the use of coloured lenses, as detailed in the Schedule of Enrolment. The test will measure participants’ comprehension and reading speed under timed conditions. Both ART-2 Test 1 passages – ‘News’ (178 words in two paragraphs; Flesch-Kincaid Grade Level 7.9) and ‘Wildlife’ (179 words in four paragraphs; Flesch-Kincaid Grade Level 7.1), will be alternatively presented to participants to avoid a learning effect. Upon initial collection of ‘experimental’ and ‘control’ lenses, participants will be asked comprehension questions on the completed ART-2 passage, to assess conceptual understanding of the passage. Each set of questions will only be asked once throughout the trial at each spectacle collection appointment, to avoid learning effects.

**Low, Mid and high spatial frequency pattern glare test:** The Pattern glare test (Institute of Optometry (i.O.O) Sales Ltd, London, UK, 2003) will measure presence and severity of cortical hyperexcitation with and without coloured lenses. Participants will be asked to focus on the horizontal striped patterns of increasing spatial frequencies (0.3, 2.3 and 9.4 cpd) at a fixed 40 cm viewing distance as per protocol discussed by Evans & Stevenson [46]. Seven questions relating to perceptual distortion visual symptoms experienced will be posed to participants. Total number of symptoms reported will be summed, where normative values >3 on the mid-spatial frequency grating, may indicate diagnosable pattern glare [46]. The series of pattern glare tests will be repeated throughout the duration of the trial to test the hypothesis that optimally selected coloured filters may reduce severity of pattern glare and thus cortical hyperexcitability.

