### Statistical analyses

The Statistical Package for Social Sciences (Version 29.0; IBM Corporation, USA), software will be used for statistical analysis of reading performance and symptom change with use of ‘experimental’ and ‘control’ precision tints. Kolmogorov-Smirnov tests will be used to assess whether the data follow a normal distribution pattern. Average-measures of Wilkins Rate of Reading Test reading speed performance with the use of ‘experimental’ and ‘control’ lenses will be assessed by repeated measures AVOVA (or the non-parametric equivalent where necessary) testing for both interventions. This will be assessed at three timepoints – baseline measures; initial spectacle collection and after 6-weeks of spectacle wear. Post-hoc analysis using repeated measures ANCOVA testing will be conducted. Covariates in statistical analysis will include: baseline reading speed, the number of errors made in each reading test, number of days spectacle lenses worn, number of hours spectacle lenses worn and number of hours completing concentrated tasks with or without the use of coloured lenses.

Clinically significant improvement noted on the WRRT, will be informed by percentage reading speed improvement with ‘experimental’ lenses, compared to baseline. To date, no validated repeatability values nor defined clinically significant improvement on the test exists in the literature. Therefore, researchers will classify participants’ reading speed improvement by two categories: (i) >5% to 15% improvement; indicating a mild clinical improvement on the WRRT and (ii) >15% improvement; indicating a moderate clinical improvement on the WRRT. These values have been derived from the consensus in the literature, whereby a stricter criterion for reading speed improvement has been applied more recently [3].

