Repeated measures ANOVA testing will also assess reading speed on secondary reading tests employed in the trial with both ‘experimental’ and ‘control’ lenses, for the Adult Reading Test (2^nd^ Edition), The Test of Word Reading Efficiency (TOWRE) and the Developmental Eye Movement (DEM) test, at baseline, upon initial spectacle collection and after six-weeks of spectacle wear. Additionally, Friedman test will assess the median change of both interventions on low, mid and high-spatial frequency pattern glare test scores. Furthermore, McNemar’s Test of Proportions will investigate changes in reading symptom frequency scores at both the start and end of the six week spectacle wear period, with both spectacle lens interventions when compared to baseline reading symptoms reported.

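### Alternating two ART-2 texts over at least five readings can reduce learning but not avoid it, so ART-2 change from baseline mixes lens effect with practice, and the stated model has no period or text term

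*Protocol article*

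**What the plan says.** Under the secondary outcome measures, the ART-2 paragraph names two prose texts: News ("178 words in two paragraphs; Flesch-Kincaid Grade Level 7.9") and Wildlife ("179 words in four paragraphs; Flesch-Kincaid Grade Level 7.1"). They "will be alternatively presented to participants to avoid a learning effect", and are read "with and without the use of coloured lenses, as detailed in the Schedule of Enrolment". Comprehension questions on the text just read are put when each pair of lenses is first collected: "Each set of questions will only be asked once throughout the trial at each spectacle collection appointment, to avoid learning effects".

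Under Statistical analyses, "Repeated measures ANOVA testing will also assess reading speed on secondary reading tests employed in the trial", ART-2 among them, with both lenses, "at baseline, upon initial spectacle collection and after six-weeks of spectacle wear". For the post-hoc ANCOVA, "Covariates in statistical analysis will include: baseline reading speed, the number of errors made in each reading test, number of days spectacle lenses worn"; the rest of that list is hours of wear and hours of concentrated tasks. Text read, reading order, period and lens sequence are not named.

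**The concern.** Learning is avoided only if each reading uses new material. Two fixed texts cannot supply that for a test given at every analysed timepoint with both lenses. The article accepts repeat use of the Developmental Eye Movement test because it is a random series of numbers. That reasoning does not carry over to ART-2, which it describes as naturalistic prose.

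Baseline is the first reading in every participant, and all lens readings come later. Any practice gain therefore points the same way as a lens benefit. The planned ANOVA includes baseline among its three timepoints, so a time effect can arise from practice alone. The texts also differ in grade level and layout, which adds a text difference of unknown sign.

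**Working it through.** **Count of readings.** The text states no number of ART-2 readings to reproduce, and the schedule figure (Fig 3) is not shown. From the timepoints in Statistical analyses, with one shared baseline:

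- readings = 1 + 2 lenses × 2 timepoints = 5
- first-time readings possible with two texts = 2, so re-readings ≥ 5 − 2 = 3
- most-read text: 5/2 rounded up = 3 readings or more

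Further readings without lenses would only raise these counts.

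**Which layouts fit.** Call the texts X and Y. Strict alternation over exactly five readings gives X, Y, X, Y, X, which puts Y at both collections. That conflicts with the comprehension rule: two question sets, each used once and at a collection visit, require different texts at the two collections. Strict alternation fits that rule if one further reading is taken after the first washout (an assumption):

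| Reading | Text | Earlier readings of that text |
|---|---|---|
| Baseline | X | 0 |
| Collection 1 | Y | 0 |
| Six weeks 1 | X | 1 |
| After washout | Y | 1 |
| Collection 2 | X | 2 |
| Six weeks 2 | Y | 2 |

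Here the first collection uses a new text and the second uses one on its third reading.

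**Change from baseline with no lens effect.** Let g be the percentage gain per earlier reading of the same text and d the percentage speed difference, Y minus X. Both are assumed: g = 1, 2 or 5; d from −5 to +5.

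- Six weeks minus baseline = [(g) + (d + 2g)]/2 = 1.5g + d/2
- With d = 0: 1.5%, 3.0%, 7.5%
- Over the range of d: from 1.5 − 2.5 = −1.0% to 7.5 + 2.5 = 10.0%
- Six weeks minus collection = (1.5g + d/2) − (g + d/2) = 0.5g, so the text difference cancels here

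The multiplier depends on layout. A five-reading order X, Y, X, X, Y also meets the comprehension rule and gives [(g) + (d + g)]/2 = g + d/2.

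**Experimental versus control.** In the six-reading layout the mean on-lens reading is (d + g)/2 in period 1 and (d + 4g)/2 in period 2, a period shift of 1.5g. Bias in the lens contrast = 1.5g × (difference in sequence sizes)/65.

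- 33/32 split: 1.5g × 1/65 = 0.02, 0.05, 0.12 points for g = 1, 2, 5
- 25/40 split: 1.5g × 15/65 = 0.35, 0.69, 1.73 points
- Under simple randomisation of 65, a split at least as uneven as 25/40 has probability of about 0.08

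**Precision.** With near-equal sequences, an unmodelled period shift δ adds about δ² to the variance of the within-person lens difference. If δ is 0.25 to 0.5 SD of that difference (assumed), variance rises by 0.25² = 6% to 0.5² = 25%.

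**The case against.** The strongest reply is that the trial's question is experimental versus control, and there the design holds up. Lens order is randomised, so a shift that follows visit order falls on both lenses almost equally. The bias at a 33/32 split is negligible. In the six-reading layout, each lens is read once on each text, so text difficulty cancels from the lens main effect. All of this stands.

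A reader might infer that alternation fully confounds collection-versus-six-weeks with text. That follows only from X, Y, X, Y, X, which the comprehension rule excludes. In the layout that fits, the text difference cancels from that comparison.

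A reader might also infer that, because each person answers comprehension questions on different texts with the two lenses, the group comparison of lenses is invalid. Within a person, text and lens are indeed tied. Across the two randomised sequences, however, text follows period and not lens, so the mean comparison is largely balanced. What remains is lost precision, and a second text that is not guaranteed to be new.

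Nor is the 0.8-grade gap (7.9 − 7.1) itself a size of bias: the documents give no conversion from grade level to reading speed.

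Finally, a separate analysis plan could add terms, and the covariate list need not be exhaustive. That tempers the point about the model. It does not affect the statement that alternation avoids learning, which the article makes itself and which the count contradicts.

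**Conclusion.** The point holds in limited form. The count of at least five readings, with at least three re-readings, rests only on the stated timepoints and a shared baseline. The claim to avoid learning is therefore wrong, and ART-2 change from baseline cannot be read as lens benefit. The size is unknown: 1.5% to 7.5% at six weeks for an assumed practice gain of 1% to 5% per re-reading, before any text difference, in a layout that Fig 3 may or may not match.

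The mean lens contrast is largely protected. The absence of a period or text term from the analysis as described costs it precision and leaves it open to sequence imbalance. ART-2 is secondary and the primary outcome is untouched, so the priority is low.

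**What to change.** 1. In the ART-2 paragraph, change *avoid* to *reduce*.
2. Log which text is read at each visit. For participants still to be enrolled, balance the starting text within lens order. The article reports 60 enrolled of 65, so this reaches about five people, and most of the gain must come from the analysis.
3. Fit the ART-2 model with lens, time and period, plus text where the layout makes it estimable. In the six-reading layout with one starting text for all, text over the lens readings coincides with the time-by-period interaction, so it can be fitted only if that interaction is left out. Do not add a linear reading number: over the lens readings it is 2, 3, 5, 6, an exact function of time and period.
4. Base ART-2 efficacy conclusions on experimental versus control, and report change from baseline as descriptive.
5. Analyse comprehension across both collections with a period (text) adjustment. Use the between-sequence comparison at the first collection as a sensitivity analysis; it is less precise because it gives up the within-person comparison.

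The cost is one or two model terms, a log field, and a slightly less favourable reading of change from baseline.

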### Statistical analyses

The Statistical Package for Social Sciences (Version 29.0; IBM Corporation, USA), software will be used for statistical analysis of reading performance and symptom change with use of ‘experimental’ and ‘control’ precision tints. Kolmogorov-Smirnov tests will be used to assess whether the data follow a normal distribution pattern. Average-measures of Wilkins Rate of Reading Test reading speed performance with the use of ‘experimental’ and ‘control’ lenses will be assessed by repeated measures AVOVA (or the non-parametric equivalent where necessary) testing for both interventions. This will be assessed at three timepoints – baseline measures; initial spectacle collection and after 6-weeks of spectacle wear. Post-hoc analysis using repeated measures ANCOVA testing will be conducted. Covariates in statistical analysis will include: baseline reading speed, the number of errors made in each reading test, number of days spectacle lenses worn, number of hours spectacle lenses worn and number of hours completing concentrated tasks with or without the use of coloured lenses.

Clinically significant improvement noted on the WRRT, will be informed by percentage reading speed improvement with ‘experimental’ lenses, compared to baseline. To date, no validated repeatability values nor defined clinically significant improvement on the test exists in the literature. Therefore, researchers will classify participants’ reading speed improvement by two categories: (i) >5% to 15% improvement; indicating a mild clinical improvement on the WRRT and (ii) >15% improvement; indicating a moderate clinical improvement on the WRRT. These values have been derived from the consensus in the literature, whereby a stricter criterion for reading speed improvement has been applied more recently [3].

Repeated measures ANOVA testing will also assess reading speed on secondary reading tests employed in the trial with both ‘experimental’ and ‘control’ lenses, for the Adult Reading Test (2^nd^ Edition), The Test of Word Reading Efficiency (TOWRE) and the Developmental Eye Movement (DEM) test, at baseline, upon initial spectacle collection and after six-weeks of spectacle wear. Additionally, Friedman test will assess the median change of both interventions on low, mid and high-spatial frequency pattern glare test scores. Furthermore, McNemar’s Test of Proportions will investigate changes in reading symptom frequency scores at both the start and end of the six week spectacle wear period, with both spectacle lens interventions when compared to baseline reading symptoms reported.

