## Methods and materials

### Study design

This study is designed as a double-masked cross-over randomised placebo-controlled trial of coloured lens efficacy in adults with symptoms of visual stress. The trial design is supported by the Standard Protocol Items: Recommendations for Intervention Trials (SPIRIT) framework (see supporting information S1 File). Participants will be evenly and randomly assigned one of two sets of coloured spectacle lenses for initial spectacle wear for a period of six weeks, followed by wear of an alternate pair of spectacle lenses for a further six weeks. Coloured spectacle lenses will differ in their chromaticity, with the ‘experimental’ coloured lenses, tinted to optimal chromaticity, which are presumed to reduce perceptual distortion symptoms, whilst ‘control’ lenses will comprise a chromaticity similar in perceptual colour appearance to ‘experimental’ lenses, to assist with masking, but differing in chromaticity, such that visual stress symptoms are neither improved nor worsened with use of tint. The ‘Control’ lenses shall therefore act as a placebo. Researchers and participants will both be masked to the spectacle lenses worn. A two week washout between periods of spectacle lens wear will be employed, so that any potential legacy effects of coloured lenses are negated.

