### Study population

#### Sample size calculation.

The Wilkins Rate of Reading Test reading speed has been used as the outcome measure for an improvement with use of coloured filters [12,13,28–31]. Sample size was calculated using statistical software (G-Power, Version 3.19.4, 2024), for an a priori within-factors repeated measures ANOVA of the Wilkins Rate of Reading Test (the primary outcome measure of this trial). A partial eta squared (${\eta \rho }^{2}$) of 0.0355 was used with a conservative small to medium effect size (f) of 0.1985. Probability of a type-1 error (α), of 0.05 and power (1−β) of 0.90 were applied. Correlation among repeat measures was assumed 0.5 and nonsphericity correction (ϵ) was held at 1.0. A sample size of 59 participants was determined appropriate for this investigation The required sample size has been increased by 10% to account for attrition. Therefore, 65 participants shall be recruited for the trial.

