#### Randomisation and blinding.

Randomisation of interventions will be conducted by the Ulster University School of Biomedical Sciences’ Clinical Trials Manager. As participant recruitment will be conducted on an ongoing basis, interventions will be randomised on a simple 1:1 basis without stratification, to ensure that if subpar enrolment is achieved, an equal number of participants will be engaged with each intervention at each timepoint in the trial. Therefore, approximately half of participants will initially receive the optimal tint whilst the other half will firstly receive the sub-optimal tint. Researchers and participants will be blinded as to which lenses are assigned throughout the duration of the trial. Both spectacle frames housing the spectacle lenses will be identical to mask researchers and participants to the intervention employed.

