### Data management

Data will be treated and stored in line with the amended Data Protection Act (2018). Reading symptom questionnaires used will have personal information attached to allow the researchers to identify participants with relevant visual stress symptoms, so that they can be contacted to participate in the trial. Once collected and analysed, each questionnaire shall be anonymised and assigned a unique participant identification number. Participants enrolled in the trial will be identified using their identification number assigned to their reading symptom questionnaire to ensure anonymity during data entry and analysis. All clinical and sensitive information written on hard-copy shall be stored in a secured filing cabinet, of which only the researchers can access. All electronic data will be stored on University-issued encrypted hardware on password-protected and encrypted data analysis programmes. Data management will comply with UK GDPR regulations. All collected data (electronic and hard copy, including data of participants who do not complete the trial) will be held for 10-years in line with university regulations. Anonymised data will be made available upon request upon cessation of the trial.

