### Ethical considerations

The protocol (version 2.0; 21/10/22) has been approved by the Ulster University, School of Biomedical Sciences Ethical Filter Committee as of 28/10/2022 (Ref: FC-BMS-189). The trial is currently listed on ClinicalTrials.gov (Ref: NCT04318106). Participants will be informed that participation in the trial is voluntary and that they can withdraw their participation at any time. Informed consent will be ascertained through a written consent form provided alongside the reading symptom questionnaire (see supporting information S3 File– consent form). Risk of adverse incident from coloured spectacle lens wear is low, but will be monitored. In the unlikely event that an adverse incident occurs, it will be reported to the project’s chief investigator [name] and through Ulster University Research Governance protocols.

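### As written, the between-lens repeated measures ANOVA uses only participants with values in both lens periods, so those who leave after the first lens add nothing to the comparison

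*Protocol article*

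**What the plan says.** The trial is a "double-masked cross-over randomised placebo-controlled trial of coloured lens efficacy" (Study design): six weeks on one lens, a two-week washout, then six weeks on the other. The order is allocated 1:1.

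For the primary outcome, Wilkins Rate of Reading Test speed, Statistical analyses states that performance with the two lenses "will be assessed by repeated measures AVOVA (or the non-parametric equivalent where necessary) testing for both interventions". It adds: "This will be assessed at three timepoints – baseline measures; initial spectacle collection and after 6-weeks of spectacle wear". SPSS version 29 is the named software. The same section gives repeated measures ANOVA to the three secondary reading tests (ART-2, TOWRE and DEM).

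On incomplete participation, the article says:
- Sample size calculation: "The required sample size has been increased by 10% to account for attrition", from 59 to 65.
- Ethical considerations: participants are told that "they can withdraw their participation at any time".
- Data management: collected data are held for 10 years, "including data of participants who do not complete the trial".
- Discussion: the numbers who dropped out or were lost to follow-up will be reported.

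The article gives the retained partial data no role in the analysis.

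**The concern.** The method named for the main comparison decides who is counted in it. In a crossover, someone who completes the first period and leaves during washout has baseline, collection and six-week values on a randomised lens. Under a complete-case ANOVA comparing the lenses, those values are not used.

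Who leaves may not be a matter of chance. Wear is voluntary and as much as the participant wishes (Spectacle wear periods and washout), so perceived benefit could plausibly affect whether a person continues. If people with a poor first-period response leave more often, more of them will have worn the control lens first. Those who remain in the control-first order are then people who did comparatively well on control, which shrinks the lens difference among completers. The same selection in the experimental-first order works the other way and cancels part of this. The net effect is what needs sizing.

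**Working it through.** **1. The plan's own figure, and what attrition does to power.** Inputs from Sample size calculation: partial eta squared 0.0355, alpha 0.05, power 0.90, correlation 0.5, nonsphericity correction 1. Three measurements are assumed, matching the three timepoints.

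- f = √(0.0355 / 0.9645) = 0.1919.
- Noncentrality λ = f² × m × N / (1 − ρ), with df 2 and 2(N − 1).
- N = 59: λ = 0.0368 × 3 × 59 / 0.5 = 13.0, power 0.901. The stated 59 is reproduced. (The printed f of 0.1985 would give 56; that is a separate matter.)
- 59 × 1.1 = 64.9, rounded to 65, as stated.
- 65 × 0.9 = 58.5. With 58 completers, λ = 12.8 and power is 0.896.
- With 20% lost, 52 completers remain and power is 0.858.

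At the planned attrition, complete-case analysis costs almost no planned power.

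**2. Who is left out.** A between-lens repeated measures ANOVA needs baseline, collection and six-week values with both lenses. The rank-based equivalent also needs complete blocks. Anyone lacking one of these values leaves the lens comparison. The head-to-head comparison and the three-month call are not among the three timepoints, so missing those removes nobody.

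**3. Possible size of bias.** The documents give no dropout by lens or by response, so this is an illustration on assumed values. Set-up: 65 randomised; baseline, first-period and second-period values with SD 1 and pairwise correlation 0.5; true experimental − control difference 0.40 SD; dropout after the first period. The likelihood estimate uses every available value, with the covariance taken as known.

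| Dropout pattern | Completers | Likelihood | Shortfall of completers |
|---|---|---|---|
| Random, 10% | 0.40 | 0.40 | none |
| Partly response-related, 10% | 0.39 | 0.40 | about 2% |
| Worst 10% on first-period change | 0.374 to 0.379 | 0.40 | 5 to 7% |
| Worst 20% on first-period change | 0.360 to 0.371 | 0.40 | 7 to 10% |

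The ranges cover pooled and sequence-averaged completer estimates. Arithmetic: (0.40 − 0.374) / 0.40 = 6.5%; (0.40 − 0.379) / 0.40 = 5.3%; (0.40 − 0.360) / 0.40 = 10%; (0.40 − 0.371) / 0.40 = 7.3%. In the worst-10% scenario about two thirds of those lost had worn control first, which is the mechanism described above.

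**4. Set against sampling error.** With SD 1 and correlation 0.5, the within-person difference has variance 1 + 1 − 2 × 0.5 = 1, so its standard error with 58 completers is 1 / √58 = 0.13. A shift of about 0.025 is 0.025 / 0.13 ≈ 0.2 standard errors.

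**5. Sensitivity to the dropout model.** A second set of scenarios used a true difference of 0.27 SD, dropout during the first period driven by the collection-visit value, and in some cases varying individual lens effects. At 10 to 19% dropout, completer estimates ran from 0.24 to 0.28. The shift was small and went in either direction.

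**The case against.** The strongest reply is that this amounts to preferring one standard method over another for a small and conditional gain. Much of it stands.

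- **Bias is not shown.** A reader might infer that lens-related dropout does bias the comparison. The article reports no dropout by lens and no link to response. Under random dropout there is no bias; under the other assumptions above it is small.
- **Not every absence counts.** A reader might infer that any missed visit removes a participant, or that non-completers' data can never be used. Only the three analysed timepoints matter. The wording of the ANOVA sentence, which speaks of testing both lenses, also allows one ANOVA per lens, in which a first-period completer stays in that lens's analysis. That reading does not rescue the comparison, because separate per-lens analyses do not test experimental against control, which is the superiority question.
- **Precision is provided for.** The 10% allowance covers it.
- **The harsher scenarios favour the remedy.** They remove exactly the worst recorded responders, so dropout depends only on observed values, which is where a likelihood analysis works by construction. If people leave because of experience that no test recorded, a mixed model is not guaranteed to correct it.
- **An analysis plan may exist.** Analysis sets, imputation and sensitivity analyses are commonly left to it, and their absence from the article is not held against it here. The complete-case restriction is different, because it follows from the method that the article itself names.

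**Conclusion.** The point holds in a limited form. As the analysis is written, participants without values in both lens periods drop out of the experimental-versus-control comparison for the primary and secondary reading tests, and nothing in the article brings their retained data back in.

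The consequence is a conditional risk of attenuation. It is about 5 to 7% of the lens difference if the worst 10% of first-period responders leave, and up to about 10% if 20% leave. It is about 2% if dropout is only partly response-related and nil if it is random. These figures rest on an assumed correlation of 0.5, a true difference of 0.40 SD and dropout after the first period; other assumptions gave small shifts in either direction. At the planned attrition the shift is about 0.2 of a standard error.

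The documents do not support saying that the trial's estimate will be biased, or that the trial is underpowered on this account: power with 58 completers is about 0.90. This is a cheap improvement to the stated method, not a fault that invalidates it.

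**What to change.** In Statistical analyses, replace repeated measures ANOVA as the main analysis of the primary and secondary reading tests with wording such as:

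*Reading-test outcomes will be analysed with a likelihood-based linear mixed model (SPSS MIXED) with fixed effects for lens, period, sequence and timepoint and a participant effect. All available measurements from every randomised participant with at least one post-baseline value will be used, with lens as randomised. The complete-case repeated measures ANOVA will be reported as a sensitivity analysis.*

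Baseline values should stay in the model, because dropout related to change from baseline is handled only if baseline is included.

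Cost: a change of analysis wording and slightly more modelling work, in software already named. No extra visits or participants are needed. The model relies on data being missing at random and does not correct dropout driven by unrecorded experience.
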